**Methods:**

This article reports the design and protocol for a cluster randomized control trial for suicide prevention and management. After the developed intervention is pilot tested in a tertiary hospital in Kerala, the intervention will be scaled up to be implemented in various tertiary hospitals in Kerala. Each hospital emergency department will be considered a cluster, and these clusters will be randomized to the intervention group and control group in a 1:1 ratio. The eligible people from the intervention clusters will undergo a baseline assessment, a structured moderate intense intervention with twelve sessions spread across 6 months by the trained social workers supervised by the Mental health team, and a follow-up assessment at the end. Participants will be recruited after obtaining consent and explaining the study. The primary outcome includes suicidality measured by the Depressive Symptom Inventory–Suicidality Subscale (DSI-SS), Depression, Anxiety and Stress Scale (DASS), MOS Social Support Survey, and Brief resilience scale (BRS).

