### Study setting

A list of NABH (National Accreditation Board for Hospitals and Healthcare) Accredited hospitals from Kerala state, India, will be prepared to select the intervention clusters. The inclusion criteria for selecting hospitals will be any NABH accredited Tertiary referral multi-speciality hospital with a minimum of 500 inpatient beds. Eligible hospitals will be randomized to intervention or control groups in a 1:1 allocation ratio. We will sign a referral agreement with the emergency department in charge and their team after explaining to them the purpose. Emergency departments of the chosen hospitals will be considered as individual clusters, and all those who presented to the emergency departments of these hospitals after serious suicidal attempts will be assessed by the professional social workers working in the department. The Social Workers will induct the people and their family members after educating them about the purpose of the study and getting informed consent. The consented people from the experimental cluster will receive the treatment as usual (TAU) plus FASE intervention, and the people belongs the control clusters will receive the treatment as usual (TAU) interventions. The stages of enrolment, intervention, and assessment can be seen in Figure 1.

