### Statistical analysis plan

#### Sample size and power calculation

A sample size of 282 will be collected from 10 clusters, with an average of 28 required from each of the 10 clusters. The clusters receiving the FASE intervention and the clusters receiving the usual care will be randomized 1:1 ratio and 28 samples will be recruited for the study allowing for a 20 % loss in follow-up rate. The Critical z is 1.64 and *R*^2^ is 0.3 with 95% power, a two-sided alpha of 5% with a cluster effect of 0.05 results in a sample size of 256. The 95% power and additional 10% respondents would allow us to maintain at least the 80% power even after the 20% loss to follow-up. Thus, we aim to recruit 282 participants for this study.

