#### Data analysis

Hard copies of data will be stored in a secure place, while soft data will be stored securely using file locks and passwords. Basic descriptive statistics will be computed for outcomes. The main effects of the interventions will be assessed on primary and secondary outcomes at different time points before and after the intervention. With the SPSS and R software, we will run the multiple regression modeling to determine the overall fit of the model and the relative contribution of each of the predictors to this variance. Multinomial Logistic Regression will be applied to study the exposure variables that are likely to contribute to the variation on the outcome variables, and discriminant analysis will be used to determine whether the clusters differ with regard to the predictors.

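### The analysis section names no method that accounts for the randomised hospitals in the FASE versus TAU comparison, although the sample size assumes a cluster effect of 0.05

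*Protocol article*

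**What the plan says.** The unit of randomisation is clear. The abstract's Methods paragraph says "Each hospital emergency department will be considered a cluster, and these clusters will be randomized to the intervention group and control group in a 1:1", and Study setting repeats it: "Emergency departments of the chosen hospitals will be considered as individual clusters".

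The sample size section takes clustering into account in principle. It states "A sample size of 282 will be collected from 10 clusters, with an average of 28 required from each of the 10 clusters", and that "a two-sided alpha of 5% with a cluster effect of 0.05 results in a sample size of 256".

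The Data analysis section sits under the article's own heading for a statistical analysis plan. It promises that intervention effects on the primary and secondary outcomes will be assessed over time, and attaches no method to that promise. It then names three methods:

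- Multiple regression: "we will run the multiple regression modeling to determine the overall fit of the model and the relative contribution of each of the predictors".
- Multinomial logistic regression, for exposure variables that may explain variation in the outcomes.
- Discriminant analysis: "discriminant analysis will be used to determine whether the clusters differ with regard to the predictors".

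The last is the only mention of clusters in that section. It names no random effect, GEE, cluster-robust variance or hospital-level summary.

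**The concern.** Arm is assigned to hospitals, so the information on FASE versus TAU lies between 10 hospitals, presumably five per arm. The article expects outcomes to be correlated within hospitals, since it plans for a cluster effect. The analysis section then commits to methods that, as usually run, treat patients as independent. The only sentence that brings in clusters asks whether hospitals differ on predictors, which does not adjust the arm comparison. Entering hospitals as fixed predictors would not help either, because arm is constant within a hospital.

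If the comparison were made by ordinary regression on patients, standard errors would be too small, confidence intervals too narrow, and the false-positive rate above the stated 5%. The trial is meant to inform policy and clinical guidelines on suicide prevention, so a nominal 5% test that is really nearer 20% would matter.

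**Working it through.** **Inputs from the article**

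- 10 clusters and 282 participants (Sample size and power calculation): 282 / 10 = 28.2 per hospital.
- 20% loss to follow-up (same section): 282 × 0.8 = 225.6, or 22.6 per hospital.
- Two-sided alpha of 5% and cluster effect 0.05 (same section). Reading 0.05 as the ICC is an assumption.

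**The plan's own figure**

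The last step reproduces: 256 × 1.10 = 281.6, rounded to 282. The 256 itself cannot be rebuilt from the stated inputs ("The Critical z is 1.64"; R-squared "is 0.3 with 95% power"), because no effect size or standard deviation is given. An overall F test for R-squared 0.3 with 1 to 20 predictors gives 33 to 89, or 78 to 209 after a design effect of 2.35. Reading 0.3 as a correlation, with a one-sided test, gives 116; multiplied by a design effect of 1 + (25.6 − 1) × 0.05 = 2.23 this is 259, which is close but needs a different reading of the text. So 256 does not show how the 0.05 was used.

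**Design effect**, DE = 1 + (m − 1) × ICC, at ICC 0.05

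- m = 28.2: 1 + 27.2 × 0.05 = 2.36; the true standard error is √2.36 = 1.54 times the unadjusted one.
- m = 22.6: 1 + 21.6 × 0.05 = 2.08; √2.08 = 1.44.

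**Type I error of an unadjusted nominal 5% test**, 2 × [1 − Φ(1.96 / √DE)]

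- DE 2.36: 2 × [1 − Φ(1.276)] = 20.2%.
- DE 2.08: 2 × [1 − Φ(1.36)] = 17.4%.

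A nominal 95% interval would therefore cover about 80% to 83%.

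**Sensitivity to the ICC** (same formula)

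| ICC | m = 22.5 | m = 28 |
|---|---|---|
| 0.01 | 7.5% | 8.2% |
| 0.02 | 10.1% | 11.4% |
| 0.05 | 17.4% | 20.1% |
| 0.10 | 26.9% | 30.8% |

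**Simulation check** (40,000 trials per setting, 5 versus 5 clusters)

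- ICC 0.05: the unadjusted test rejected in 20.3% (m = 28) and 17.1% (m = 22). A t-test on cluster means with 8 degrees of freedom rejected in 4.8% and 5.0%.
- ICC 0: the unadjusted test rejected in 4.8% to 4.9%, so there is no inflation.

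**With baseline adjustment**

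Simulated ordinary regression adjusted for baseline used 10 clusters of 23, ICC 0.05 at both times, individual-level correlation 0.5 and 8,000 replicates. It rejected in 24%, 17.5%, 13.5% and 9% when the hospital-level correlation between baseline and follow-up was 0, 0.5, 0.8 and 1. The article gives neither correlation, so 9% to 24% is a range under assumptions.

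**The case against.** The strongest reply is that the article does not state an analysis on individual patients. It gives no unit of analysis and no variance estimator, and multiple regression can be fitted with cluster-robust errors or on hospital means. The sentence on intervention effects has no method attached. The three named methods are described in terms of predictors, exposures and differences between clusters, which fits the first objective (the contribution of psychosocial factors) as well as the arm comparison. A fuller analysis plan may exist, and degrees-of-freedom corrections are often left to one.

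Much of this stands. A reader might infer that the plan's p-values and intervals will certainly be wrong; the text supports this only conditionally. A reader might also fault multinomial regression for not suiting a summed score, or discriminant analysis for giving no treatment effect, but the text does not clearly give them that job. Nor does the article propose a clustered analysis with a normal reference: its critical z appears only in the sample size section.

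What does not stand is that this is detail left for elsewhere. The article has its own analysis plan section and commits to named methods in it. None of them, in standard form, fits the cluster design or the cluster effect assumed in the preceding section.

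**Conclusion.** The point holds in conditional form. The plan randomises hospitals and budgets for a cluster effect, yet it names no method that carries hospital into the FASE versus TAU comparison and does not say which model makes that comparison.

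The size rests on two assumptions: that the comparison is run as ordinary regression on patients, and that 0.05 is the ICC. The type I error is then about 17% to 20% instead of 5%. It falls to about 7.5% to 8% at an ICC of 0.01 and disappears at zero, though the article itself plans for a non-zero effect. Baseline adjustment does not remove the problem at an ICC of 0.05: about 9% to 24% over the hospital-level correlations tried. The documents do not show that an unadjusted analysis will be done, only that nothing in the stated plan rules it out.

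**What to change.** State in Data analysis that the primary FASE versus TAU comparison is of the DSI-SS total at 6 months, by a method that accounts for hospital. Any one of these would do, if named in advance:

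- a linear mixed model with arm, baseline DSI-SS and a random hospital intercept, using Kenward-Roger or Satterthwaite degrees of freedom;
- an equivalent GEE with a small-sample correction;
- a t-test on hospital means with 8 degrees of freedom.

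Report the arm difference, its 95% confidence interval and the estimated ICC. Use the same approach for the DASS, MOS and BRS scores. Table 1 also lists DSI-SS at 3 months, so say how that measurement enters. Keep multinomial regression and discriminant analysis for the exploratory psychosocial-factor objective.

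The change is to wording and analysis code; R is already planned and no new data are needed. The real cost is wider intervals and lower power. The article gives no effect size, so as an illustration only: for an assumed standardised difference of 0.45, an individual-level calculation on 256 patients gives 95% power. A cluster-level t-test at ICC 0.05 gives 58% with 28 per hospital and 54% with 22.5. The sponsor should restate power alongside the revised analysis.

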#### Primary outcome

The primary outcome will be the total suicidality score measured by the Depressive Symptom Inventory–Suicidality Subscale (DSI-SS) (21). The DSI-SS is a 4-item self-report questionnaire designed to assess the frequency and intensity of suicidal ideation and impulses in the past 2 weeks. The scale measured suicidality on a four-point scale ranging from 0 to 3, with higher scores indicating greater severity of suicidal ideation. DSI-SS scores exhibited good internal consistency, ω = 0.90 [95% CI =0.89–0.91], convergent validity (rs = 0.52–0.74), discriminant validity (rs = 0.12–0.27) (22).

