##### Depression, anxiety, stress

DASS 21 is a shortened version of Depression, Anxiety and stress scale developed by Lovibond and Lovibond (23). Participants will be asked to rate their levels of depression, anxiety and stress on a 4-point severity/frequency scales over the past week. Subscales include seven questions each which is computed to obtain total scores for depression, anxiety and stress. Higher scores on the scale indicate high severity of symptoms. The DASS 21 tool exhibits high internal consistency, with alpha coefficients of 0.85, 0.81, 0.81 respectively for depression, anxiety and stress scales and is a tested valid in Indian population (24). The study will look for a decrease in depression scores from baseline to follow-up among participants in both groups to test the effectiveness of the intervention.

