##### Resilience

The Brief Resilience Scale (BRS) measures the ability to bounce back from stressful situations in life (26). BRS is a 6-item questionnaire measuring resilience on a five-point scale ranging from one (low resilience) to five (high resilience). The scale exhibits good internal consistency with Cronbach's α = 0.71 (27).

The project team will measure customer satisfaction regarding the services at the end of the follow-up measurement using a set of questions measuring overall efficiency, professionalism, accessibility, and the overall administration of benefits.

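### The outcomes are defined as scale scores, but the analysis section applies multinomial logistic regression to them without defining any categories, and ties no model to the treatment effect

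*Protocol article*

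**What the plan says.** The Primary outcome section reads: "The primary outcome will be the total suicidality score measured by the Depressive Symptom Inventory–Suicidality Subscale (DSI-SS". It describes the instrument as follows: "The DSI-SS is a 4-item self-report questionnaire designed to assess the frequency and intensity of suicidal ideation and impulses in the past 2 weeks". Responses are on a "four-point scale ranging from 0 to 3, with higher scores indicating greater severity of suicidal ideation".

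The secondary scales are presented in the same way. For DASS-21: "Subscales include seven questions each which is computed to obtain total scores for depression, anxiety and stress". For resilience: "BRS is a 6-item questionnaire measuring resilience on a five-point scale ranging from one (low resilience) to five (high resilience". The MOS survey is described as a 19-item questionnaire, with no scoring rule. No cut point or category is given for any of the four instruments.

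The Data analysis section makes three separate statements about modelling outcomes:

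- on the treatment effect, with no model named: "The main effects of the interventions will be assessed on primary and secondary outcomes at different time points before and after the intervention";
- on multiple regression: "we will run the multiple regression modeling to determine the overall fit of the model and the relative contribution of each of the predictors";
- on multinomial regression: "Multinomial Logistic Regression will be applied to study the exposure variables that are likely to contribute to the variation on the outcome variables".

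**The concern.** Multinomial logistic regression models membership of unordered classes. To apply it to a DSI-SS total, someone must cut the score into classes, and the model then disregards that one class is worse than another. Because the article contains no cut points, they would be set at analysis, possibly with the results in view.

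The section also leaves the source of the treatment effect unclear. Multiple regression would give one mean difference between arms. A multinomial model would give one arm coefficient per non-reference class: two with three classes, and twelve if each of the 13 possible totals were its own class. Nothing says which of these is the trial's result.

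This is separate from clustering. Adding hospital effects to a multinomial model would not make it suitable for a score.

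**Working it through.** **Scale of the outcome.** Four items scored 0 to 3 give a maximum of 4 × 3 = 12, so the total runs from 0 to 12 and has 13 ordered levels.

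**The plan's own sample size.** Sample size and power calculation gives 256 plus 10%: 256 × 1.10 = 281.6, rounded to 282. That step reproduces. The 256 itself can be neither reproduced nor refuted, because no effect size, standard deviation or odds ratio is given. Any statement about power under one model or another therefore needs an assumed effect.

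**Benchmark effect (assumption).** Take the effect for which an analysis of the score has the stated 95% power at two-sided 5% with 256 patients, with clustering treated as already absorbed:

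- noncentrality = 1.960 + 1.645 = 3.605
- d = 2 × 3.605 / √256 = 0.451

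This uses 1.96 because the article calls alpha two-sided. The printed critical z of 1.64 is a separate matter.

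**Same effect after categorising.** Assume normal scores with arm means at ±d/2 and cuts at quantiles of the pooled distribution. Let p1k and p0k be the class probabilities in the two arms and mk their average. The likelihood-ratio test of arm in a multinomial logit with K classes has K − 1 degrees of freedom and noncentrality

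λ = 256 × Σk [p1k ln(p1k/mk) + p0k ln(p0k/mk)].

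Power is the probability that a noncentral chi-square with that λ exceeds the 5% critical value. For the median split the class probabilities are 0.589/0.411 in one arm and 0.411/0.589 in the other, so λ = 512 × [0.589 ln(0.589/0.5) + 0.411 ln(0.411/0.5)], about 8.18 before rounding.

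| Form of the outcome | df | λ | Critical value | Power |
|---|---|---|---|---|
| Score | 1 | 12.99 | 3.84 | 0.95 |
| Median split | 1 | 8.18 | 3.84 | 0.82 |
| Three equal classes | 2 | 10.17 | 5.99 | 0.82 |
| Classes of 50/30/20% | 2 | 9.70 | 5.99 | 0.80 |
| Four equal classes | 3 | 11.02 | 7.81 | 0.80 |
| Five equal classes | 4 | 11.47 | 9.49 | 0.78 |

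**Check on an integer score.** This simulation used a rounded 0–12 score, latent SD 3, mean 5, 113 per arm (282 less 20%, halved), no clustering and 4000 runs per setting:

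| Assumed d | Score (t test) | 3 classes | 4 classes | 13 classes |
|---|---|---|---|---|
| 0.30 | 60% | 43% | 39% | 30% |
| 0.375 | 79% | 61% | 57% | 43% |
| 0.45 | 91% | 78% | 75% | 61% |

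With mean 3 the figures are within about 3 points.

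**Where the result does not carry over.** Many 6-month totals may be 0. With 128 per arm, classes 0 / 1–3 / 4–12 and no clustering, three assumed shapes gave:

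| Assumed distribution | Score (t test) | 3 classes |
|---|---|---|
| 40% against 60% zeros, same non-zero scores | 63% | 83% |
| 40% against 58% zeros plus a small severity shift | 79% | 77% |
| Floor-censored normal | 89% | 84% |

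So the loss is consistent for roughly normal scores but can vanish or reverse with a heavy floor.

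**The case against.** The strongest reply is that the multinomial sentence does not concern the treatment test. It speaks of exposure variables, which fits the first listed objective on psychosocial contributors to self-harm. The treatment effect has its own sentence, and a model suited to a score is already named. The secondary outcomes also include customer satisfaction and use of services, whose scale is not fixed and which may be categorical. Cut points are a detail that a condensed article may leave to the full plan.

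Much of this stands. A reader might infer that the primary treatment test is multinomial and so cannot have the stated 95% power. The documents do not support that: the section never assigns the multinomial model to that comparison, the basis of 256 is not given, and sizing for a logistic model is not excluded. A reader might equally infer that categorising always costs power; the zero-heavy cases show otherwise.

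What does not stand is that nothing needs correcting. The sentence does not limit the model to categorical outcomes or exclude study arm from the exposures. The multiple regression sentence is framed around model fit and the contribution of predictors, so it is no more clearly the treatment analysis. Even as an exposure analysis, a nominal model is a poor choice for ordered scores. A fuller plan could supply cut points, but that would not make the model suit an outcome defined as a total.

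**Conclusion.** The point holds as a mismatch between the defined outcomes and a stated method, together with an unresolved question of which model yields the treatment effect. It rests on the text alone and needs no assumption about effect size.

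The consequence for power is conditional. If the multinomial model were used for FASE plus TAU against TAU, scores were roughly normal and the true effect were d ≈ 0.45, power would be about 78–82% instead of 95% with a median split or three to five classes. The effect size is back-solved, clustering is taken as absorbed, and the direction is not assured when many scores are 0. The figures illustrate what is at risk; they do not estimate this trial's power.

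**What to change.** In Data analysis, state that the FASE plus TAU versus TAU effect on the 6-month DSI-SS total is estimated as a single difference from a regression for a numeric score, adjusted for DSI-SS at T0 and allowing for clustering by hospital. Apply the same form to the 6-month DASS-21, MOS and BRS scores, each adjusted for its own baseline. Table 1 already schedules all four instruments at T0 and T2. The clustering term belongs in the sentence: a plain regression on arm would not suit a trial randomising 10 hospitals.

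Add an ordinal model on the uncategorised DSI-SS total as a sensitivity analysis if scores pile up at 0.

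Remove multinomial logistic regression for these scale scores, or limit it to a named secondary or exploratory analysis of outcomes that are truly categorical, with categories fixed in advance.

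The cost is a wording change, with no new data, visits or patients. The downside is that per-category odds ratios for the scale outcomes would no longer be reported.

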#### Sustainability and cost-effectiveness

Resource utilization will be recorded on all aspects of intervention implementation. Social Workers' salary, printed intervention manuals and brochures, telephone recharge expenses, train hall rent, transportation, scribbling pad and recording facility will be provided and the expenses will be documented to evaluate the cost-effectiveness of the project. Apart from 10 professional social workers employed in each cluster, no additional human resource expenses are expected as we focus on task sharing with the existing health workforce in the hospitals for implementing and supervising the intervention. The follow-up intervention by the second-year psychiatric social work students as part of their field placement reduces the human resource cost. Therefore, we will not calculate this cost within the trial. We will call or make home visits (if needed), to the participants to ensure they do not incur any additional telephone recharge costs or travel expenses. Per person cost will be calculated by total expenses divided by the number of people who received the FASE intervention. The anticipated savings from loss of life or the hospitalization costs, which the families largely incur due to repeated attempts alone, would likely offset the costs of paying social workers' salaries. If this approach proves promising in Kerala, more rigorous testing and nationwide dissemination could be possible with the support of more than 540 Schools of Social Work, most of which have field placement agreements with nearby hospitals. This family-focused model could be customized to suit the socio-cultural context of the locality. This model can be incorporated into the social work curricula through MSW internship training and post-graduate practice. Within a few years, India would have general hospital-based mental health services where virtually none currently exist. A national social work mental health organization could codify the credentialing of practice standards.

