## Materials and methods

### Aim of the study

The research has two aims, to build evidence on the effectiveness of an Attachment-Based Family Therapy and Resource linkage model to prevent suicide in people presenting with self-harm behaviors in emergency departments at tertiary hospitals in Kerala; Secondly, to evaluate the efficacy of the process of delivery of services and assess the cost-effectiveness of sharing the care task with the social work trainees supervised by the mental health team, through a continuum of care from critical health care to family-based services. The research team has been developing this model for over the past 2 years. The results of this feasibility trial would provide insights into the model's effectiveness in responding to multiple and complex psychological and social precipitants to deliberate self-harm that are currently ignored in general health services.

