### Objectives of the study

The major objectives of the study include

Evaluate the contribution of psychosocial factors to self-harm behavior and the role of psychosocial aspects in preventing suicide.Develop the ABFT and Community Linkage model for the prevention of suicide in a group of people presenting with self-harm behavior at emergency departments;Compare the treatment (TAU) as the usual plus FASE intervention with the TAU using a cluster RCT design framework;Develop the systems and processes appropriate to deliver the services for people presenting with self-harm behavior at emergency to integrate a psychosocial intervention that would have broad relevance and application nationally and in low and middle-income countries;Assess the proposed model's cost-effectiveness for managing self-harm behavior focused on a seamless continuum of care from acute health to community services.

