### Outcome

Study outcomes are assessed at baseline and 6-month follow-up. Demographic characteristics measured at baseline include age, gender, marital status, education, occupation, and family income. The following information on the clusters selected will be collected: number of hospital beds, patients, social workers, primary treatment modalities, and the average length of stay at the hospital. Measurement domains and time points are summarized in Table 1.

**Table 1 T1:** Measurement domains and data collection time points.

**Variable**	**Dimensions included**	**Measurement tool**	**Data collection time points**		
			**Baseline (T0)**	**3 months (T1)**	**6 months (T2)**
Demographic assessment	Age, sex, marital status, education, occupation, and family income		✓		
Suicidality	Suicidal thoughts and ideation	Depressive Symptom Inventory–Suicidality Subscale (DSI-SS)	✓	✓	✓
Depression, anxiety, stress	Depression, anxiety, stress	DASS 21	✓	✓	✓
Social support	Emotional support, tangible support, affectionate support, positive social interaction	The MOS social support survey	✓		✓
Resilience	Resilience	The Brief Resilience Scale (BRS)	✓		✓
Customer satisfaction		Questionnaire			✓

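### The stated costing is a FASE-only average per recipient that leaves out trainee labour and is tied to no effect, so it understates delivery cost and does not answer the cost-effectiveness aim

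*Protocol article*

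**What the plan says.** Cost-effectiveness appears twice as a purpose of the research. Under *Aim of the study*, the second aim includes to "assess the cost-effectiveness of sharing the care task with the social work trainees supervised by the mental health team". Under *Objectives of the study*, a listed objective is "Assess the proposed model's cost-effectiveness for managing self-harm behavior focused on a seamless continuum of care from acute health to community services".

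The comparison is an add-on design. Under *Study setting*: "The consented people from the experimental cluster will receive the treatment as usual (TAU) plus FASE intervention". Control clusters receive TAU alone.

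The method is in *Sustainability and cost-effectiveness*:
- Scope of recording: "Resource utilization will be recorded on all aspects of intervention implementation". The listed items are social workers' salaries, printed materials, telephone charges, hall rent, transport and recording.
- Staff: beyond the project's social workers, no extra personnel cost is expected, because existing hospital staff implement and supervise.
- Student-delivered follow-up: it is said to lower personnel cost, and then "Therefore, we will not calculate this cost within the trial".
- Statistic: "Per person cost will be calculated by total expenses divided by the number of people who received the FASE intervention".
- Expected offset: "The anticipated savings from loss of life or the hospitalization costs, which the families largely incur due to repeated attempts alone" are said to be likely to balance the salaries.

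Table 1 ("Measurement domains and data collection time points") lists demographics, DSI-SS, DASS 21, MOS social support, BRS and satisfaction. *Secondary outcome* also names appropriate use of primary care and community resources, with no tool or time point.

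**The concern.** A cost-effectiveness result needs a difference in cost between arms set against a difference in effect. The stated statistic has neither. It is a mean programme cost in the FASE arm.

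The aim concerns handing care to trainees under supervision, yet trainee delivery is the input expressly left out, and supervision is expected to cost nothing extra. The statement that savings would balance salaries depends on events that the listed measurements do not capture.

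The same section looks ahead to national dissemination through more than 540 schools of social work. A reader weighing that step would have a delivery cost that is too low and a saving that was never observed. Event data not collected during follow-up cannot be recovered reliably afterwards.

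**Working it through.** The article states no cost or cost-effectiveness figure, so there is none to reproduce. The check compares aim with method, counts sessions, and asks what the listed measures can show.

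**1. Aim against method**

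| Needed for the aim | What the article provides |
|---|---|
| Cost of trainee delivery | Expressly not calculated |
| Cost of supervision | No added cost expected |
| Cost difference, FASE + TAU against TAU | FASE expenses only |
| Effect linked to cost | None named |
| Repeat attempts and admissions, for the offset | No listed measure |

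**2. Sessions by provider (Table 2)**

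- Social workers, direct: 2
- Trainees, by telephone: 8 (family therapy) + 2 (linkage) = 10
- Trainee share: 10/12 = 83% of sessions

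**3. Number of uncosted sessions**

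The target of 282 agrees with its own last step in *Sample size and power calculation*: 256 × 1.10 = 281.6. Assuming equal arms and full delivery:

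- Total 282: 282/2 = 141 FASE participants; 141 × 10 = 1,410 trainee sessions, against 141 × 2 = 282 social-worker sessions.
- Total 158 (the target in *Study procedure*): 158/2 = 79; 79 × 10 = 790 against 79 × 2 = 158.

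Supervisor time comes on top. The 83% is the same under both totals.

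**4. Possible effect on session labour**

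No unit cost or session length is given. Assume a trainee session is worth a fraction *w* of a social-worker session. Full session labour relative to counted session labour is then (2 + 10*w*)/2:

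- *w* = 0: 1.0
- *w* = 0.25: 2.25
- *w* = 0.5: 3.5
- *w* = 1: 6.0

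These ratios apply to session labour only. Total cost also includes materials, telephone, transport and the salary time social workers spend on recruitment and assessment, so total cost would rise by less.

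**5. Can the offset be seen?**

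DSI-SS covers ideation and impulses over the past two weeks, not attempts. As an illustration, assume a 6-month repeat-attempt risk under TAU of 5% to 15% and a risk ratio of 0.8 to 0.5. Attempts averted among 141 people = 141 × risk × (1 − risk ratio):

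- Low end: 141 × 0.05 × 0.2 = 1.4
- High end: 141 × 0.15 × 0.5 = 10.6

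No listed outcome would register any of these.

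**The case against.** The strongest reply has several parts.

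- **FASE is added to TAU, and DSI-SS is measured in both arms with the same tools.** TAU delivery cost largely cancels, so a programme cost per DSI-SS point could be formed. This stands. A reader might infer that the aim cannot be answered at all, and the document does not support that. But no such ratio is planned, and it would still omit trainee labour and downstream service use.
- **Salaries are counted.** This also stands. A reader might infer that FASE will look almost free; with social workers' salaries among the recorded expenses, that does not follow. The cost is understated, not absent.
- **The denominator.** A reader might think that dividing by recipients rather than by everyone enrolled in FASE clusters flatters the result. It cannot: recipients are at most as many as those enrolled, so the per-person figure is equal or higher.
- **Placement time is unpaid, and scale-up would use the same placements.** Leaving it out is disclosed and could suit a provider perspective. But no perspective is stated, and sharing care with trainees is the subject of the aim. Reporting both versions meets this.
- **Table 1 is not exhaustive, since service use is named as a secondary outcome.** That is partly right. The item is limited to primary care and community resources, has no tool or time point, and does not extend to repeat attempts or admissions.
- **A condensed article may leave detail to a fuller document.** That would excuse silence on perspective or ratio. Here the article fixes a formula and rules out a cost, so a fuller document would have to contradict it.
- **The offset is only a projection, and wider use is made subject to further testing.** True, which limits the harm. It is still an expectation that the trial is not set up to check.

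**Conclusion.** The concern holds in this form. The stated method is a FASE-only average per recipient. It leaves out the labour behind 10 of 12 sessions, expects no added cost for supervision, and links cost to no effect. It therefore understates delivery cost and does not answer the aim.

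That it understates cost rests on one assumption: that trainee and supervisor time has some value above zero. By how much cannot be known from the document. The 83% is a share of sessions, not of cost. The 1,410 sessions assume full delivery and 282 participants; with 158 the figure is 790. The labour ratios and averted-attempt counts are illustrations on assumed inputs.

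The expected offset cannot be tested with the listed outcomes. The point concerns the second aim and leaves the primary DSI-SS comparison untouched. It should be settled before recruitment.

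**What to change.** Preferred change:

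1. Log trainee and supervisor time per session. Report per-person cost with and without a value on that time, and state the rate used, for example the project social workers' salary rate.
2. At the 3- and 6-month contacts shown in Table 1, ask both arms about repeat self-harm, emergency visits and admissions, and record deaths, since the offset claim relies on them.
3. Report incremental cost per DSI-SS point by randomised arm, with an interval that respects the clustering.

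Alternative: restate the aim and objective as a description of delivery cost, and remove the statement that savings would offset salaries.

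The cost is a time log, a few minutes per contact, and a less favourable cost figure. The alternative needs only a change of wording.
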